### Sample size considerations

#### **
*Estimating the prevalence of extra-NICE symptoms in patients consulting UK general practices*
**

We have modeled the study using the CAPER (Cancer Prediction in Exeter) lung database [12,15], which contains all primary care consultations, symptoms, and investigations in the 2 years before diagnosis for a 5-year cohort of 247 lung cancer cases, to estimate the potential benefit of expanded chest X-ray use. Smokers aged over 60 years make up 3.2% of the UK population, and we estimate that in a 1-year period, 24% of these would present with extra-NICE symptoms only; that is, 0.768% (or 42 per year in an average practice of 5,500 patients). Hence, if we were to recruit 26 practices (each with a patient population of 5,500) and recruited patients over an average of 6 months (a 12 month recruitment period with practices opening at different points throughout that period), we could get an estimate of this with confidence intervals of 0.70 to 0.83% from a patient-year population of 71,500 (26 × 5,500 × 0.5).

#### **
*Estimating the proportion of those with extra-NICE symptoms who will agree to participate*
**

If we were to find a prevalence of extra-NICE symptoms of 0.768% per year then, from the above, we might find 550 patients eligible for the study. Studies conducted at the Wales Cancer Trials Unit have found a 70% consent rate of eligible patients into trials. We could get an estimate of this with confidence intervals of 70 to 74% in this study.

#### **
*Estimating the proportion of those who agree to participate and who are diagnosed with lung cancer*
**

If 386 (70%) eligible patients consented to participate in the trial, then we could get 95% confidence intervals of 0.9 to 3.9% around an estimate of 2.4% (from CAPER lung database) of those who will be diagnosed with lung cancer.

It was decided to try to open all practices to recruitment for at least 12 months during the running of the trial, so as to avoid any selection bias caused by symptom seasonality.

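### Expected counts and intervals assume an average of 6 months' recruitment per practice, but the plan then aims for at least 12 months and restates nothing

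*Protocol article*

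**What the plan says.** All of this is in the protocol article under Sample size considerations.

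- The yearly yield is stated as "that is, 0.768% (or 42 per year in an average practice of 5,500 patients").
- The calculation is conditional: "if we were to recruit 26 practices (each with a patient population of 5,500"). The time factor of 0.5 is explained as practices having "recruited patients over an average of 6 months (a 12 month recruitment period with practices opening at different points throughout that period").
- From this come the "confidence intervals of 0.70 to 0.83% from a patient-year population of 71,500 (26 × 5,500 × 0.5") and the statement that "we might find 550 patients eligible for the study".
- The consent assumption is that studies at the trials unit "have found a 70% consent rate of eligible patients into trials". The lung cancer interval then starts from "If 386 (70%) eligible patients consented to participate in the trial".
- The closing paragraph, which gives symptom seasonality as its reason, says "It was decided to try to open all practices to recruitment for at least 12 months during the running of the trial".

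The Study design section plans about 20 practices in south-east Wales and a small number elsewhere, which is compatible with 26. The article gives no cap on recruitment and no reduced number of practices that would go with the longer opening.

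**The concern.** The counts and intervals rest on half a year per practice, while the opening time finally adopted is at least a full year. The two descriptions also differ in kind. Practices that open at staggered points inside a 12-month recruitment period average about 6 months each. They cannot all be open for 12 months unless the overall period is extended or all of them start together.

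The trial is a feasibility pilot, and its expected numbers of eligible patients, participants and cancers are the figures that a funder or oversight committee would hold beside the observed ones. They also set the expected volume of questionnaires, data linkage and practice follow-up. If they describe a shorter recruitment time than the one planned, the benchmark is too low.

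**Working it through.** **Inputs** (Sample size considerations, except the number of practices in step 2)

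- Annual prevalence of extra-NICE symptoms: 0.032 × 0.24 = 0.00768. Check: 0.00768 × 5,500 = 42.2 per practice per year, as stated.
- Practices and list size: 26 × 5,500.
- Time open: 0.5 year in the calculation, at least 1 year in the closing paragraph.
- Consent 0.70; lung cancer among participants 0.024.

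**Formulas**

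- Patient-years = practices × 5,500 × years open
- Eligible = patient-years × 0.00768
- Recruited = 0.70 × eligible
- Cancers = 0.024 × recruited
- 95% interval = p ± 1.96 × √(p(1 − p)/n)

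**Step 1: reproduce the stated figures at 6 months**

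- 26 × 5,500 × 0.5 = 71,500, as stated.
- 71,500 × 0.00768 = 549 (stated 550).
- 0.70 × 549 = 384, or 385 from 550 (stated 386). The difference is rounding.
- 386 × 0.024 = 9.3, about 9 cancers.
- Prevalence, n = 71,500: 0.704 to 0.832% (stated 0.70 to 0.83%).
- Lung cancer, n = 386: 0.87 to 3.93% (stated 0.9 to 3.9%).
- Consent, n = 550: 66.2 to 73.8% (stated 70 to 74%). The upper limit agrees and the lower does not. That is a separate error, unrelated to the opening time.

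So the 6-month basis does generate the stated counts and two of the three intervals.

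**Step 2: the same inputs at 12 months**

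The 20-practice column takes the approximate south-east Wales number in Study design alone, as a low case.

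| | 26 practices, 6 months | 26 practices, 12 months | 20 practices, 12 months |
|---|---|---|---|
| Patient-years | 71,500 | 143,000 | 110,000 |
| Eligible | 549 | 1,098 | 845 |
| Recruited | 384 | 769 | 591 |
| Lung cancers | 9 | 18 | 14 |
| Prevalence interval | 0.70–0.83% | 0.72–0.81% | 0.72–0.82% |
| Consent interval | 66.2–73.8% | 67.3–72.7% | 66.9–73.1% |
| Lung cancer interval | 0.87–3.93% | 1.32–3.48% | 1.17–3.63% |

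Counts rise by 143,000/71,500 = 2.0 with 26 practices and by 110,000/71,500 = 1.54 with 20. Interval widths scale with 1/√n: 1/√2 = 0.71, about 29% narrower with 26 practices, and 1/√1.54 = 0.81, about 19% narrower with 20. For consent, the comparison is with the recomputed 66.2 to 73.8%. The printed 70 to 74% is too narrow for its own inputs.

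**Step 3: could the stated totals still hold at 12 months?**

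Keeping 71,500 patient-years with a full year per practice needs 71,500/5,500 = 13 practices. The article describes no such number.

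**The case against.** The strongest reply is that nothing is miscalculated. The counts are conditional illustrations of precision, the 12 months is something the trial will try to achieve, and the two can stand together. If the aim is met, precision is better than stated, and this section rests no power claim on 386. Much of that is right. The arithmetic is sound on its stated basis (apart from the consent limit), the direction is conservative, and the annual inputs (0.768%, 42 per practice, 70%, 2.4%) do not depend on the opening time. What the reply does not explain is why a decision already taken is absent from every figure that depends on it.

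Three stronger readings are tempting, and the article does not support them.

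- A reader might infer that every figure is wrong by a factor of two. Only the counts double, and only with 26 practices; the intervals narrow by about 29%.
- A reader might infer that recruitment could end at 386 and so defeat the seasonality purpose. The article never calls 386 a target, cap or stopping point; it is the number used for one interval. Rules for closing recruitment are commonly left to a full protocol, which is not shown.
- A reader might set 386 against 1,098 and conclude that true participation would be 35% (386/1,098) while appearing to be 70%. That assumes that all 1,098 are identified and that recruitment halts at 386, and the article states neither. Under Primary outcome measures, participation is recruited patients over logged eligible patients, and prevalence uses the logged count over list size. Low consent or poor identification would therefore show in those outcomes whatever planning total is quoted.

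**Conclusion.** The point holds as an internal inconsistency in the planning figures. The expected counts belong to an average of 6 months per practice, and the adopted aim is at least 12. If the aim is met, the stated 71,500 patient-years, 550 eligible and 386 recruited, and the 9 or so cancers that follow, are too low by a factor of about 1.5 (20 practices) to 2 (26 practices). The intervals are wider than the planned design would give, apart from the consent interval, whose printed lower limit is wrong for another reason.

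This rests on the article's own prevalence, consent and lung cancer rates, on an average list of 5,500, and on the 12-month aim being achieved. Opening beyond 12 months would widen the gap; falling short of 12 would reduce it. The validity of the analysis is not affected. What is affected is the benchmark for expected recruitment and workload.

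**What to change.** In Sample size considerations, restate the expected eligible, recruited and lung cancer counts and the three intervals for the planned number of practices and a 12-month opening, and give the present 6-month figures as the minimum case. With 26 practices that means 143,000 patient-years, 1,098 eligible, 769 recruited and about 18 cancers, with intervals of 0.72–0.81%, 67–73% and 1.3–3.5%. If 550 and 386 are meant to stand, state instead the number of practices or the recruitment cap that keeps them. Reconcile the description of staggered opening within a 12-month period with the 12-month aim in the same edit.

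The cost is a recalculation and a few sentences. Nothing in the conduct of the trial changes beyond what has already been decided.

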### Method of randomization

Randomization will take place centrally at the Bristol Randomised Trials Collaboration using either an automated telephone or a secure online service. Participants will be randomized using minimization with a random element. This will ensure balanced treatment allocation by a number of clinically important factors: GP practice, age (<75 or ≥75 years), and COPD diagnosis. Randomization will have an allocation ratio of 1:1.

### Outcome measures and statistical analysis

The primary analysis will be intention to treat.

#### **
*Primary outcome measures*
**

The primary outcome measures are as follows.

• The prevalence of extra-NICE symptoms in patients consulting a UK general practice. Participating practices will be asked to log a count of all eligible patients. The prevalence will be calculated as the total number of eligible patients logged by the participating practices divided by the total number of patients on their lists.

• The proportion of those who agree to participate. This will be known from trial recruitment, and calculated as the total number of patients recruited by the participating practices divided by the total number of eligible patients logged by them.

• The proportion of those that are diagnosed with lung cancer. This will be obtained from the UK National Lung Cancer Audit Database (LUCADA; available from the NHS Information Centre) and the general practices. It will be calculated as the total number of participating patients found to have lung cancer divided by the total number of patients recruited. A statistical comparison of the proportion in each arm will be made.

#### **
*Secondary outcome measures*
**

We will also assess the following secondary outcome measures

• Of those patients diagnosed with lung cancer, we will assess stage at diagnosis, performance status, and the proportion of patients receiving radical treatments. This will be obtained from LUCADA and the general practices, and proportions will be presented overall and by trial arm.

• Anxiety/depression that may be caused by unnecessary or no chest X-rays. This will be measured using the Hospital Anxiety and Depression Scale (HADS) [32] and informed by the qualitative interviews. This will be presented overall and by trial arm.

• Assessment of false-positive (suspicion of cancer on X-ray but no subsequent cancer diagnosis within 6 months) and false-negative (no suspicion of cancer on the X-ray but diagnosis of lung cancer within 6 months) rates for the chest X-rays. This will be obtained from LUCADA and the general practices, and proportions will be presented overall and by trial arm.

• Cost-effectiveness of extra-NICE. This will be measured by a Client Service Receipt Inventory (CSRI), the ICECAP (O) (Investigating Choice Experiments for the Preferences of Older People (ICEPOP) Capability measure [33], and the EQ-5D-3 L (EuroQol 5 Dimensional Health State Questionnaire). The CSRI completed by the patient will be compared against data about resource use available from the GP to ascertain the best method of capturing these data in the full trial.

The following processes will be reviewed and refined during the workshop at the start of the trial, during qualitative interviews, and continuously throughout the trial by the trial management group (TMG): 1) the best way to train GPs to identify and recruit eligible patients into the trial; 2) the most effective method of presenting the trial (and randomization) to patients and 3) barriers to recruitment and how can we overcome them,

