### Participant eligibility

Eligible patients will be identified within general practices, either during consultations, in chronic obstructive pulmonary disease (COPD) clinics or by retrospective searches of the records of the previous week’s consultations. To be eligible to be included in the trial the patient must meet all of the following criteria: 1) age over 60 years, 2) smoker or ex-smoker (any duration) with 10 or more pack-years of smoking (assessed using http://smokingpackyears.com/. or by dividing the number of cigarettes smoked per day by 20 and multiplying by the number of years smoked), and 3) has given written informed consent; and at least one of the following criteria: 1) a new or altered cough of any duration reported to primary care or 2) increased breathlessness or wheezing (whether or not associated with purulent sputum).

None of the following categories of patients can be included in the trial: 1) patients who qualify for urgent referral for chest X-ray under NICE guidelines that is, hemoptysis, or any of the following unexplained or persistent (that is, lasting more than 3 weeks) symptoms or signs: cough, chest/shoulder pain, dyspnea, weight loss, chest signs, hoarseness, finger clubbing, features suggestive of metastasis from a lung cancer (for example, in brain, bone, liver or skin), or cervical/supraclavicular lymphadenopathy; 2) patients who have had a chest X-ray or CT scan of the chest in the previous 3 months; 3) patients who need a chest X-ray within the following 3 weeks for reasons other than those listed above; or 4) patients previously diagnosed with cancer who have a life expectancy of less than 1 year.

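### The prevalence outcome divides logged patients by list size with no time term, although it is planned as an annual rate on patient-years

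*Protocol article*

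**What the plan says.** The protocol article treats this quantity in two places.

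*Sample size considerations* builds it as a yearly figure. It starts from "Smokers aged over 60 years make up 3.2% of the UK population", adds that "we estimate that in a 1-year period, 24% of these would present with extra-NICE symptoms only", and arrives at "0.768% (or 42 per year in an average practice of 5,500 patients". The scenario is conditional: "if we were to recruit 26 practices (each with a patient population of 5,500", with recruitment averaging 6 months per practice because practices open at staggered points in a 12-month period. The stated interval of 0.70 to 0.83% is then taken "from a patient-year population of 71,500 (26 × 5,500 × 0.5". The last paragraph of that section changes the opening plan, with symptom seasonality as the reason: "It was decided to try to open all practices to recruitment for at least 12 months during the running of the trial".

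*Outcome measures and statistical analysis*, under the primary outcome measures, fixes the calculation. Practices log a count of all eligible patients, and the prevalence is the total number of "eligible patients logged by the participating practices divided by the total number of patients on their lists". Neither time nor a counting window appears in this definition.

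**The concern.** The planned quantity is a rate per year. The defined quantity is a cumulative count over a head count. The two differ by a factor equal to the average logging time in years, and the article does not fix that time at one year.

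*Main research question* lists this prevalence first among the clinical information the pilot must supply for planning the full trial. It determines how many practices, open for how long, are needed to reach the approximately 1,900 lung cancers named there. If the ratio is reported as defined and read against 0.768%, a difference in how long pilot practices stayed open would look like a difference in how common the symptoms are. The error would pass directly into the size of the full trial.

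**Working it through.** **Inputs** (*Sample size considerations* unless noted): 3.2% of the population are smokers over 60; 24% of these present in a year; 26 practices of 5,500 patients; 6 months open on average; 70% consent; 2.4% diagnosed with lung cancer. From *Main research question*: approximately 1,900 cancers.

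**1. The plan's own figures.**
- Annual rate: 0.032 × 0.24 = 0.00768, or 0.768% per year.
- Per practice: 0.00768 × 5,500 = 42.2 per year (stated 42).
- Patient-years: 26 × 5,500 × 0.5 = 71,500.
- Expected eligible: 71,500 × 0.00768 = 549 (stated 550).
- Wald 95% CI: 0.00768 ± 1.96 × √(0.00768 × 0.99232 / 71,500) = 0.704% to 0.832% (stated 0.70 to 0.83%).

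All reproduce. The interval was therefore calculated on patient-years. With 143,000 in place of 71,500 it would be 0.72 to 0.81%.

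**2. The outcome formula on the same scenario.** The list total is 26 × 5,500 = 143,000. The ratio is 549/143,000 = 0.384%, with Wald 95% CI 0.35 to 0.42%. This is half the planned value, and the interval excludes it.

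**3. General form.** With a constant rate, the formula returns 0.768% × (list-weighted mean months open / 12).

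| Mean months open | Result | 95% CI | Source of duration |
|---|---|---|---|
| 6 | 0.384% | 0.35 to 0.42% | sample-size scenario |
| 12 | 0.768% | 0.72 to 0.81% | lower bound of the later aim |
| 15 | 0.96% | 0.91 to 1.01% | assumed, for illustration |

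**4. What it could do to the full trial** (illustration from the article's own inputs). Eligible patients needed: 1,900 / (0.024 × 0.70) ≈ 113,100. Practice-years of 5,500 patients:
- at 0.768%: 113,100 / 42.24 ≈ 2,680
- if 0.96% were read as annual: 113,100 / 52.8 ≈ 2,140
- if 0.384% were read as annual: 113,100 / 21.12 ≈ 5,350

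**5. Repeat presenters.** The article does not say whether a person presenting twice is logged once. If each person is counted once, the cumulative count grows more slowly than time. Assume a closed list and a constant hazard that gives 24% in one year. Over 15 months the proportion is then 1 − 0.76^1.25 = 29.0%, so the formula gives 0.032 × 0.290 = 0.93% instead of 0.96%. Dividing that by 1.25 years gives 0.743% per year, slightly below 0.768%. Person-time alone is therefore not a complete remedy beyond a year; the counting rule has to be stated as well.

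**The case against.** The strongest reply is that the 6-month average belongs to a conditional sample-size scenario that the article then moves away from. Under the later decision, a practice open for exactly 12 months gives 0.768% by the written formula. This stands: a reader might infer that the trial as run would report half the true rate, and the article does not support that. It does not remove the point, because the decision is an aim with a lower bound, no upper bound and no common window. Practices may exceed it or miss it.

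It can also be said that the result is not lost. With opening and closing dates, one division converts the ratio to a rate, and the authors already reason in patient-years. That also stands, and it limits the seriousness. No randomised comparison is affected. But the article states the formula explicitly, so this is not a detail left to another document. An analysis plan that used patient-years would depart from the published definition.

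The linear scaling assumes a constant rate, while the article itself is concerned with seasonality. The 15-month value is therefore an illustration, not a forecast.

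A reader might go further and note that *Participant eligibility* lists "3) has given written informed consent" among the criteria, and infer that the logs hold only consenters, so that the participation proportion would be 100% by construction. The article does not support that reading. *Sample size considerations* sets 550 eligible against 386 consenting. *Data collection* (Screening) has practices record eligible and consenting numbers separately. The second primary outcome divides recruited by eligible. The log is clearly meant to count patients before consent.

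**Conclusion.** The point holds. As defined, the first primary outcome is not the annual rate it was planned as, and it coincides with that rate only when list-weighted logging time averages 12 months. The discrepancy is a factor of 0.5 on the sample-size scenario (0.384% against 0.768%). Under the later aim it is smaller and of unknown direction: upward for practices open beyond 12 months, by a factor of 1.25 at an assumed 15 months, and downward for practices that fall short. These sizes take the article's 0.768% as the true rate, a rate constant over the year, and no loss of count from repeat presenters.

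This is a correctable mismatch between a stated formula and the quantity it is meant to estimate. *Trial status* records that recruitment was still under way at submission, so it could be settled before analysis.

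**What to change.** State the time basis in the definition of the first primary outcome. Either of two forms would do:

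- **Preferred:** count each person once within a fixed 12-month window per practice and divide by list size. This gives an annual figure directly, covers all seasons equally, and avoids the downward drift shown in step 5.
- **Where practices log for other durations:** divide by the sum over practices of list size × logging time, report per year, and state how repeat presenters are counted.

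Report the logging period with the estimate, so that it can be set against 0.768% per year and scaled to the full trial. The cost is small: one changed sentence and a record of each practice's opening and closing dates. List sizes are already needed for the formula as written. The article does not say whether the dates are already held, so that should be checked. If persons are to be counted once, the logs must also allow repeat presenters to be recognised.

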### Data collection

#### **
*Screening*
**

The number of eligible patients and the number of those who consented will be recorded by each general practice on screening logs.

#### **
*Baseline data*
**

Patient name, NHS number, Trial number, and their address will be collected to facilitate data linkage with routine datasets and administration of postal questionnaires (see below). This patient identifiable information will be sent by fax at the general practice to a secure fax at the Wales Cancer Trials Unit (WCTU) by the practice staff as soon as possible after the patient is randomized. The original consent form will then be stored in the Investigator Site File at the practice.

The following data will be collected on a Case Report Form (CRF) (using non-carbon copy paper) completed by staff at the general practice at the time of recruitment: trial number, patient initials, date of birth, gender, ethnicity, socioeconomic status, and educational level; co-morbidity (Charlson Index); venue for determination of eligibility; primary reason for presenting; ex-smoker or current smoker, number ofpack years, and the quit date for ex-smokers; presence of pre-existing lung disease; date of previous chest X-ray in the preceding 12 months; and presenting symptoms and duration.

The ICECAP(O), HADS, EQ-5D-3 L and CSRI will be given to the patient to complete at the time of randomization.

#### **
*Two months after randomization*
**

The ICECAP (O), HADS, EQ-5D-3 L, and CSRI will be posted to the patient at home to complete and return in a stamped addressed envelope. Patients will also be invited to give open comments about their experience on the trial. Staff at WCTU will check first with the patient’s GP to ensure that they are still alive before sending the questionnaires to the patient’s home address. If the patient returns the completed questionnaires, then they will be sent a £5.00 voucher as thanks. A reminder letter will be sent if no response is received within 2 weeks, and a telephone call reminder will be made if there is no response within 4 weeks [34]. A score on the completed HADS questionnaires of either less than 16 for anxiety or less than 11 for depression will trigger letters indicating the high scores to both the patient and their GP.

#### **
*During the trial*
**

General practices will be asked to append an additional sheet onto the chest X-ray request forms or letters for the patients randomized to either arm of the trial. This sheet will highlight that the patient is part of a trial, and will ask the radiology department to fax a copy of the chest X-ray result to the WCTU secure fax. In the case of missing forms, the GP practice will be contacted and asked to fax this to WCTU.

#### **
*Twelve months after randomization*
**

LUCADA will be used to collect the following data by data linkage: date of diagnosis of lung cancer; lung cancer stage at diagnosis; date of resection; WHO performance status at diagnosis; and date and cause of death.

Additionally, 12 months after randomization is completed, general practices will be sent a list of the patients that they have enrolled into the trial and asked to return the following information to WCTU: 1) a completed CRF with the following data for those patients: health resource use because being enrolled into the trial; and follow-up of any abnormal/indeterminate chest X-rays (for example, any repeat X-rays performed, and results of any biopsies); 2) a print-out (from the practice computer system) of all consultations with GPs and nurses, all prescriptions, and all results of GP-initiated investigations.

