## Trial status

At the time of manuscript submission, this trial was still in the patient recruitment phase.

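### The HADS alert rule is reversed: low scores trigger the high-score letter, and respondents at or above both cut-offs get none

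*Protocol article*

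**What the plan says.** The rule is in the Protocol article, Data collection, under the two-month follow-up. It says that a HADS score "less than 16 for anxiety or less than 11 for depression will trigger letters indicating the high scores to both the patient". The same sentence gives the content and recipients of the letters: they "will trigger letters indicating the high scores to both the patient and their GP".

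HADS appears again under Outcome measures and statistical analysis, as the secondary outcome for "Anxiety/depression that may be caused by unnecessary or no chest X-rays". The reporting plan there is "This will be presented overall and by trial arm". That section gives no cut-off. The 16 and 11 appear only in the Data collection sentence.

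**The concern.** The trigger and the letter point in opposite directions. A score below a cut-off sets the letter off, yet the letter tells the patient and the GP that the score is high. The sentence shows the conflict by itself, so no outside knowledge of HADS scoring is needed. The comparison is spelled out in words for both scales, so it is not a symbol lost when the PDF was read.

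What is at stake is participant welfare. The article treats distress as a possible consequence of having an unnecessary X-ray and of having none, so the alert matters in both arms. Followed as written, the rule would alarm people who are low on both scales and pass over those who are high on both. Under Trial status the article reports that, at submission, "this trial was still in the patient recruitment phase". A correction made then could still have applied to questionnaires not yet returned.

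**Working it through.** Let A be the anxiety score and D the depression score.

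**Rule as written.** Letter if A < 16 or D < 11. Negating this, no letter if A ≥ 16 and D ≥ 11.

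**Rule reversed.** There are two candidates, and the article does not settle which is meant:
- inclusive: letter if A ≥ 16 or D ≥ 11
- strict: letter if A > 16 or D > 11

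**Written and inclusive rules by cell**

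| Respondent | As written | Reversed, inclusive |
|---|---|---|
| A < 16, D < 11 | letter | none |
| A < 16, D ≥ 11 | letter | letter |
| A ≥ 16, D < 11 | letter | letter |
| A ≥ 16, D ≥ 11 | none | letter |

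The two rules disagree in exactly two cells: low on both and high on both. A respondent high on only one scale still gets a letter under the written rule.

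**Score pairs near the boundary**

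| A / D | As written | Inclusive | Strict |
|---|---|---|---|
| 0 / 0 | letter | none | none |
| 15 / 10 | letter | none | none |
| 16 / 10 | letter | letter | none |
| 15 / 11 | letter | letter | none |
| 16 / 11 | none | letter | none |

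The last three rows show why the boundary needs stating: the inclusive and strict versions treat scores of exactly 16 or exactly 11 differently.

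**Illustrative size if the literal wording were followed.** The base is the scenario in Sample size considerations: "If 386 (70%) eligible patients consented to participate in the trial". The rest are assumptions, not figures from the article: 60% to 100% return the two-month questionnaire, 70% to 95% of respondents are below both cut-offs, and 1% to 5% are at or above both.

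- Questionnaires returned: 386 × 0.60 = 232 to 386 × 1.00 = 386.
- Low on both, wrongly sent a letter: 386 × 0.60 × 0.70 = 162 to 386 × 1.00 × 0.95 = 367.
- High on both, sent no letter: 386 × 0.60 × 0.01 = 2.3 to 386 × 1.00 × 0.05 = 19.3.

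**The case against.** The strongest reply is that this is a wording slip with an obvious intent. The reference to high scores tells any reader which direction was meant, and staff preparing such a letter for someone scoring 0 on both scales would be likely to notice. A journal article condenses the full protocol, and the operative letter procedure is held by the trials unit and is not shown. Nothing in the article uses the cut-offs to define an outcome or an analysis, so no inference depends on them. The counts rest on assumed return rates and score shares, and 386 is a conditional scenario in a precision calculation, not a stated recruitment target.

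Most of this stands. The likely cause is a slip, no mishandling is shown, inference is untouched, and the counts illustrate scale without being evidence of harm. Two things remain. The article does not leave this rule to another document: it states it, and states it wrongly, in the methods, for a procedure that reaches patients and their GPs. And knowing the intended direction does not settle how scores exactly at 16 or 11 are handled, which only the trial team can say.

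**Conclusion.** The point holds with high confidence. The alert rule contradicts itself as written, and nothing elsewhere in the article corrects it. It should be fixed because it governs a participant-welfare procedure, but it does not threaten the trial's conclusions.

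The logical result rests on no assumption: under the literal rule, only respondents at or above both cut-offs get no letter. The size does rest on assumptions. Within the ranges used it is about 162 to 367 false letters and about 2 to 19 missed respondents, provided the literal text was followed. It is zero if the trials unit's procedure already runs in the opposite direction.

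**What to change.** Reword the sentence so that an anxiety score of 16 or more, or a depression score of 11 or more, on a completed HADS prompts the letter to patient and GP. The inclusive form is a proposal: the clinical team should confirm whether 16 and 11 themselves count as high, and the text should say so.

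Separately, confirm that the trials unit's trigger procedure uses this direction. Only if it does not should the questionnaires already returned be rechecked, so that respondents high on both scales are identified and letters sent in error are corrected.

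The cost is one corrected sentence and one check of the procedure. Design, sample size and analysis stay as they are.
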